### Randomization and blinding

One hundred and eighty people with Parkinson’s will be randomly allocated to either the intervention group (integrated rehabilitation program (IR)) or the control group who will participate in life skills information sessions (LS). Randomization will be stratified according to each referral source in permuted blocks of 6, 8 and 10 by an independent private trials coordination organization. Those involved in recruitment and assessment will be blind to group allocation.

### Interventions

The IR program and LS sessions will be delivered in participants’ homes by therapists trained in the appropriate intervention at a standardized training session conducted by the study team. Both IR and LS programs will run for six weeks. Interventions will comprise one 60 minutes session per week delivered by a therapist, plus a 60 minutes “homework” session performed by the participant following pre-printed but individualized worksheets. Physiotherapists will deliver the IR intervention and allied health professionals including occupational therapists and speech pathologists will run the LS sessions. Both the IR program and the LS sessions will occur in addition to participants’ usual healthcare.

#### Integrated rehabilitation program

The IR participants will undertake a structured but individually tailored program of (i) progressive resistance strength training (PRST), (ii) movement strategy training (MST) and (iii) falls prevention education. This protocol integrates elements from interventions previously detailed by Morris et al. [27]. Written advice to therapists will assist them to schedule the time allocated between the various activities. Strength training exercises will be prioritized over other activities if a participant is unable to complete all three components within the allotted time for each session (60 minutes). The “homework” program will repeat activities from the therapist’s session for that week, modified to participant need and any safety issues. Pre-printed forms will be used to report the activities undertaken by each individual at each session and the amount of perceived effort used. Participants will record homework performance on similar forms. These data will enable later evaluation of adherence to and compliance with the interventions. Participants will be asked at each session whether they experienced any negative side effects of treatment such as muscle soreness or joint stiffness from the previous session, whether it required any health service attendance and the results recorded.

Participants will be given an intervention pack containing a booklet with the exercises pictured and described, a modified Rate of Perceived Exertion scale (mRPE) [56], an exercise log book (used to monitor compliance with the homework program), a sheet of frequently asked questions about strength training and a booklet on falls prevention [57]. They will also receive a standard help sheet from Parkinson’s Victoria listing resources for participant or caregiver support.

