### Life skills training

The control group’s LS sessions will be of equivalent duration to the IR program, with the same therapist-participant contact time and a weekly self-directed but structured “homework” session. The program will consist of a series of guided education and discussion sessions based on topics of interest. These will be selected by each participant from a pre-defined syllabus to optimize retention and interest. Topics include information on: relaxation; energy conservation; fatigue management; voice and communication; swallowing and diet; travel advice; and memory skills. No session content will relate to physical activity, exercise, walking, or falls risk education. Participants in the LS group will also be given a general intervention pack containing the standard help sheet from Parkinson Victoria, Australia. Ethics required us to provide a generic falls information sheet also.

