### Outcome measures

#### Primary

The primary outcome measure will be falls, defined as “an unexpected event in which the participants comes to rest on the ground, floor or lower level” [59]. Falls will be monitored during the 6 weeks intervention and for 12 months thereafter, consistent with the recommendations of the ProFaNE consensus group . Participants will mark all falls on the day they occur on a falls calendar, [60]or mark a month without falls by ticking a box marked “I had no falls”. Pre-paid envelopes will be provided for the return of each month’s calendar sheet. Injurious falls, defined as a fall requiring medical attention or any healthcare utilization, will be marked with a yellow sticker. Telephone calls will be used to remind participants who have not returned their monthly sheet. Calls will also investigate each injurious fall using a set questionnaire that examines the health and economic sequelae of the fall based on data from Medicare Australia, self-reported health care utilization and out-of-pocket expenditure.

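### Non-fall side effects and resulting health service attendances are, as written, asked about at each session in the rehabilitation arm only, so they have no comparator

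*Protocol article*

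**What the plan says.** The harm enquiry stands in the section Integrated rehabilitation program of the protocol article. That section opens with "The IR participants will undertake a structured but individually tailored program" and later says "Participants will be asked at each session whether they experienced any negative side effects of treatment such as muscle soreness or joint stiffness". The question looks back to the last visit, and the sentence closes with a second enquiry, namely "whether it required any health service attendance and the results recorded".

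The Interventions section, which covers both arms, gives the schedule: "Both IR and LS programs will run for six weeks", with a weekly one-hour therapist visit and an hour of homework. It contains no side-effect question.

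The section Life skills training describes the control sessions as "of equivalent duration to the IR program, with the same therapist-participant contact time", with matched weekly homework. It lists the topics and the information pack. It gives no question on symptoms or on health service attendance.

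Falls are handled differently. The primary outcome section says "Falls will be monitored during the 6 weeks intervention and for 12 months thereafter", without restriction to one arm. Injurious falls are followed up by telephone with a questionnaire on health and economic consequences, and the Statistical analysis section has them analysed by the same methods as falls.

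**The concern.** The trial compares strength training at a high level of perceived exertion with a control programme that has no physical activity content. Musculoskeletal complaints are the obvious tolerability question, and the article shows that its authors expect them. Soreness, stiffness and visits to a health service can also be expected in an ageing population with Parkinson's disease that does no exercise programme.

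If symptoms are asked about at every visit in one arm and not in the other, the IR count mixes background complaints with programme effects, and nothing in the trial separates the two. A reader of the final report who sees IR events beside an empty or sparse LS column would take an ascertainment difference for a treatment difference. At stake is how the tolerability of the programme is interpreted. The falls result is not at stake.

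**Working it through.** The article states no figure on this point, so none can be reproduced. The check is a comparison of sections, followed by one illustration.

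**Who is asked.** The word for those asked is simply participants, so its scope has to be read from context. The section opens with the IR participants. Its next paragraph uses the same unqualified word for people who receive a booklet of exercises, which only IR participants do. The Life skills training section, by contrast, names the LS group when it means the control arm. The sentence therefore refers to IR participants.

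**Side by side, as written:**

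| Item | IR | LS |
|---|---|---|
| Therapist visits | 1 per week × 6 weeks = 6 | 1 per week × 6 weeks = 6 |
| Session question on side effects | at each session | none described |
| Session question on resulting attendance | at each session | none described |
| Falls calendar, six weeks plus 12 months | yes | yes |
| Telephone questionnaire after an injurious fall | yes | yes |

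**Planned enquiries.** With 90 per group (Power calculation and sample size), the ceiling is 90 × 6 = 540 enquiries in IR and 90 × 0 = 0 described for LS. Missed sessions and drop-out would lower the first number.

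**Other routes of capture.** The telephone calls investigate injurious falls, and the Economic evaluation section draws its medical costs from those same falls. A non-fall symptom or attendance in LS has no described route into the data.

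**Illustration.** The article gives no background rate. Assume that a proportion *p* of participants would report at least one such symptom over six weeks whatever their arm, and that each would be recorded when asked. The expected number of IR reporters with no programme effect at all is 90 × *p*:

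- *p* = 0.10: 90 × 0.10 = 9
- *p* = 0.20: 90 × 0.20 = 18
- *p* = 0.40: 90 × 0.40 = 36

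The number solicited in LS is 0 in each case. The range is an assumption and shows only how unequal ascertainment can look like harm.

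**What is not touched.** The Statistical analysis section plans no comparison of session-level side effects between arms. The costs listed under Economic evaluation are programme delivery, therapist training and care after injurious falls. Session-reported attendances are not among them.

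**The case against.** The strongest objection is that this rests on silence in a condensed article. The article nowhere says that LS participants are not asked. Its account of the LS arm is one short paragraph that also leaves out session forms and adherence records, and the full protocol may hold an LS harm form. This limits confidence but does not remove the point. The article does not merely omit harm collection: it states the enquiry and places it in one arm, while the paragraph common to both arms lacks it.

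Three stronger readings are tempting, and the document does not support them.

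- A reader might infer that harms in general have no concurrent control. Falls, and injurious falls with their healthcare use, are recorded in both arms, and injurious falls are compared between them. Blinded assessors also measure disability and quality of life in both arms.
- A reader might infer that side effects cannot be attributed to the programme at all. The question concerns effects of treatment following the previous session, so a single report can still be judged on its merits. What is lost is the comparison of rates.
- A reader might infer that the cost-effectiveness ratio is distorted. That would follow only if session-reported attendances were added to IR costs, and the article does not list them.

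It is also fair to object that the 9 to 36 is only an assumed rate multiplied by 90, and that not every background complaint would be reported as a side effect of treatment. Both points stand, which is why the figure serves as illustration only.

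Finally, adding an item to the LS form alone would leave the arms answering different questions, because the IR wording presupposes treatment and names soreness and stiffness. This also stands and shapes the fix.

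**Conclusion.** The point holds in a limited form. As the article is written, non-fall side effects and any resulting health service attendance are actively sought at up to six sessions per participant in IR and at none in LS, although both arms have the same visits. The IR counts have no randomised background rate beside them, and any tabulation by arm would be biased against IR.

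The size of that bias cannot be derived from the document. Under the assumed 10% to 40% background rate it would be 9 to 36 IR reporters out of 90 without any programme effect.

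The conclusion assumes that the section's heading and context fix who is asked, and that no LS harm form exists in a document not shown. The primary falls analysis, the comparison of injurious falls and the planned cost-effectiveness ratio are unaffected. The change is worth making because it is cheap and bears on how tolerability is reported, but the trial's main result does not depend on it.

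**What to change.** Move the enquiry into the Interventions section, as a procedure common to both arms. Use one neutrally worded item on both the IR and the LS session forms: any new or worse symptom since the last session, and whether it needed a health service attendance. Ask it at every session in both arms and tabulate the answers by arm. The question on soreness and stiffness can stay as an additional IR tolerability item, reported for IR alone and not set against LS. If LS participants are in fact already asked the same question, one sentence saying so in Interventions or Life skills training settles the matter.

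The cost is slightly longer LS paperwork at six visits that a therapist already makes, and a small rewording of the IR form. No extra visits are needed. One limitation remains: the therapists know which programme they deliver and come from different professions in the two arms, so elicitation may still differ somewhat even with identical wording. The report should say so.

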#### (a) Progressive resistance strength training

Strength training will focus on the major muscle groups integral to functional gait, balance and transfers, such as quadriceps, glutei, hip abductor and trunk muscles. The five exercises incorporated are: sit to stand; step-ups; heel raises; standing hip abduction; and trunk extension and rotation. The training protocol will follow guidelines published by the American College of Sports Medicine to ensure optimal training stimulus [56]. Therapists will train participants how to perform the exercises safely, focusing on correct form. They will also assist participants to understand the level of perceived exertion required, i.e. hard – very hard (5 – 7 on the Modified Rating of Perceived Exertion [56]. Exercise resistance may be progressed by altering starting position or via a weighted vest or resistance bands. Participants will complete 2 sets of 8 to 12 repetitions of each exercise, with 2 minutes rest between each set, aiming for a minimum of three different strengthening exercises each session.

#### (b) Movement strategy training

MST will be based upon the principles previously described in detail by Morris [2,26,27] emphasizing evidence-based training techniques for people with Parkinson’s. These include the ability of participants to initiate and execute everyday functional activities, facilitated as appropriate by the use of cues (visual, auditory, cognitive or proprioceptive) and attentional strategies, such as conscious attention strategies, such as conscious attention. This training approach uses practice of everyday activities such as standing up, moving from chair to chair, standing and reaching, walking, walking while carrying objects or turning and bed mobility. Activities will be selected and progressed according to each participant’s individual ability, needs and home environment. For more detail on possible progression, see Morris et al. (2011) [27].

#### (c) Falls education

Education about falls prevention will be based upon the content of the booklet “Don’t Fall for It! Falls Can Be Prevented” [57]. The Commonwealth of Australia has adopted and published this guide for the prevention of falls in older people. It comprises advice on various aspects of falls and safety, such as an overview of risk factors, keeping mobile, medication, vision, feet and footwear, and safety in the home environment. Each IR session will reflect the booklet content, with particular reference as to how that topic may be relevant to the individual participant.

### Life skills training

The control group’s LS sessions will be of equivalent duration to the IR program, with the same therapist-participant contact time and a weekly self-directed but structured “homework” session. The program will consist of a series of guided education and discussion sessions based on topics of interest. These will be selected by each participant from a pre-defined syllabus to optimize retention and interest. Topics include information on: relaxation; energy conservation; fatigue management; voice and communication; swallowing and diet; travel advice; and memory skills. No session content will relate to physical activity, exercise, walking, or falls risk education. Participants in the LS group will also be given a general intervention pack containing the standard help sheet from Parkinson Victoria, Australia. Ethics required us to provide a generic falls information sheet also.

### Assessments

All assessments will be performed in the participant’s home by a trained physiotherapist blind to group allocation. Participants will be reminded not to disclose their treatment or group allocation to the assessor. Assessments will occur in the week prior to therapy commencing (T1), in the week after six weeks’ therapy (T2) and 12 months after therapy completion (T3). Difference between T1 – T2 assessments will allow evaluation of the immediate effect of therapy, while T2 to T3 difference will determine whether the IR program has a longer term effect. Each assessment will include the MDS-UPDRS [53], PDQ39 [54,55] and the EuroQol EQ-5D^TM^[58]. Medications and their dosage will be recorded on each test occasion.

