**Methods/design:**

180 community living people with PD will be randomly allocated to receive either a home-based integrated rehabilitation program (progressive resistance strength training, movement strategy training and falls education) or a home-based life skills program (control intervention). Both programs comprise one hour of treatment and one hour of structured homework per week over six weeks of home therapy. Blinded assessments occurring before therapy commences, the week after completion of therapy and 12 months following intervention will establish both the immediate and long-term benefits of home-based rehabilitation. The number of falls, number of repeat falls, falls rate and time to first fall will be the primary measures used to quantify outcome. The economic costs associated with injurious falls, and the costs of running the integrated rehabilitation program from a health system perspective will be established. The effects of intervention on motor and global disability and on quality of life will also be examined.

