#### Secondary

Secondary outcome measures include changes in motor disability, global disability and quality of life. Changes in motor disability and global disability will be compared from pre- to post-therapy (T1 to T2) and from T2 to 12 months after therapy ceases (T3), using respectively the motor section III of the MDS-UPDRS [53,61] and the full MDS-UPDRS. The MDS-UPDRS is the current version of the original UPDRS [62], augmented and revised in line with the findings of its review taskforce (MDS, 2003), and represents the gold standard in PD assessment. Quality of life will be evaluated on the same occasions, using the disease-specific PDQ-39 [54,55] which has demonstrated validity, reliability and sensitivity. The widely used generic EQ-5D [58] will allow comparison of quality of life with non-PD populations [63].

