#### Secondary

All variables will be examined using descriptive statistics to ensure they meet the assumptions necessary for parametric analysis. If not, non-parametric equivalent analyses will be used. Repeated measures ANOVA with planned comparisons will examine between group differences in the secondary outcome variables and investigate the effects of the intervention.

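### For the secondary outcomes, the longer-term effect is assigned to the T2–T3 change, which measures whether a benefit is retained, not whether one is present 12 months after therapy

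*Protocol article*

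**What the plan says.** The protocol article (Assessments) sets three home visits: T1 in the week before therapy, then "in the week after six weeks’ therapy (T2) and 12 months after therapy completion (T3"). It gives each question its own contrast. For the short term: "Difference between T1 – T2 assessments will allow evaluation of the immediate effect of therapy". For the long term: "while T2 to T3 difference will determine whether the IR program has a longer term effect". The MDS-UPDRS, PDQ-39 and EQ-5D are collected at each visit.

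Outcome measures, Secondary, uses the same two intervals for motor and global disability, which "will be compared from pre- to post-therapy (T1 to T2) and from T2 to 12 months after therapy ceases (T3"). For the quality-of-life scales it says only "Quality of life will be evaluated on the same occasions".

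Statistical analysis, Secondary, names the model: "Repeated measures ANOVA with planned comparisons will examine between group differences in the secondary outcome variables". The planned comparisons are not listed.

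The Abstract (Methods/design) gives the purpose: the blinded assessments "will establish both the immediate and long-term benefits of home-based rehabilitation". It names no contrast, so it states the aim and does not repeat the problem. No section names a T1–T3 change or a between-group comparison at T3.

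**The concern.** The long-term question is whether people given IR are better off than controls 12 months after therapy ends. A change that starts at T2 starts after the treatment has already acted. Any benefit gained during the six weeks is in the T2 value and is subtracted out. What is left is how the groups diverge or converge after therapy stops.

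For a six-week programme followed by 12 months without study therapy, a good result would be a benefit that is kept or only partly lost. The named contrast is zero in the first case and points towards control in the second. Only a benefit that grows after therapy ends would register as a longer-term effect in favour of IR. At stake is the long-term reading of the disability and quality-of-life results. There is also a risk of choosing after the fact between two contrasts that can have opposite signs.

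**Working it through.** The article gives no figure for this contrast, so there is nothing to reproduce. The check is algebra, followed by an illustration on assumed values.

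**Algebra.** Let D2 and D3 be the IR minus control differences in means at T2 and T3, coded so that negative values favour IR. Randomisation makes the expected difference at T1 zero.

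- T1–T2 contrast: D2 − 0 = D2
- T2–T3 contrast: D3 − D2
- T1–T3 contrast: D3 − 0 = D3

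The long-term question is about D3. With d for the size of the benefit:

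| Course of the benefit | D2 | D3 | T2–T3 contrast | T1–T3 contrast |
|---|---|---|---|---|
| Never any benefit | 0 | 0 | 0 | 0 |
| Fully maintained | −d | −d | 0 | −d |
| Half lost | −d | −d/2 | +d/2 (favours control) | −d/2 (favours IR) |
| Fully lost | −d | 0 | +d (favours control) | 0 |
| Late benefit only | 0 | −d | −d | −d |

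Rows one and two have the same T2–T3 value, so this contrast alone cannot tell full retention from no effect at all. In the half-lost row the two contrasts are equal in size and opposite in sign.

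**Illustration.** Inputs from Power calculation and sample size: 90 per group, 20% drop-out, alpha 5%. Evaluable per group: 90 × (1 − 0.20) = 72. Assumed, because the article does not give them: a two-sided test, equal SD at each visit (set to 1), d of 0.3 or 0.5 SD, and within-person correlation ρ of 0.5, 0.7 or 0.8 between any two visits.

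- SD of a change score: √(2(1 − ρ)). For ρ = 0.7 this is √0.6 = 0.775.
- Standard error of a between-group difference in change: 0.775 × √(2/72) = 0.129.
- T1–T3, benefit maintained at d = 0.5: 0.5/0.129 = 3.87, and 3.87 − 1.96 = 1.91, so power is 97%.
- T2–T3, benefit maintained: 0/0.129 = 0, so the rejection rate is 5%, which is alpha.
- Half lost at d = 0.5: T2–T3 is +0.25 and T1–T3 is −0.25. Each is significant in 49% of trials, in opposite directions.

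Power for a fully maintained benefit over the assumed range:

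| d (SD) | ρ | T1–T3 | T2–T3 |
|---|---|---|---|
| 0.3 | 0.5 | 44% | 5% |
| 0.3 | 0.7 | 64% | 5% |
| 0.3 | 0.8 | 81% | 5% |
| 0.5 | 0.5 | 85% | 5% |
| 0.5 | 0.7 | 97% | 5% |
| 0.5 | 0.8 | 99.7% | 5% |

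The T1–T3 column moves with the assumptions. The T2–T3 column does not: its expected value is zero for any effect size, SD, correlation or sample size.

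**T3 adjusted for T1 against T1–T3 change.** Both estimate D3 under randomisation. With equal SDs the variances are proportional to 1 − ρ² and 2(1 − ρ), a ratio of (1 + ρ)/2. That is 0.75, 0.85 and 0.90 for ρ = 0.5, 0.7 and 0.8, so the adjusted difference is the more precise of the two.

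**The case against.** The strongest reply is that the formal analysis is the repeated measures ANOVA, not the sentence under Assessments. With three visits in the model, a maintained benefit gives group differences of 0, −d and −d, and a group-by-time test responds to that. A T3 comparison may also be among the unlisted planned comparisons, and an article may leave that list to a fuller document. This stands in part: T2–T3 is not shown to be the only long-term test. But the article does not give the long-term question to the group-by-time test. That test would also respond to a benefit seen at T2 and gone by T3, so it does not isolate D3. The only contrast the text assigns to the long-term question is T2–T3.

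A second reply is that the two contrasts are meant to be read as a pair: a T1–T2 gain with no T2–T3 loss describes a retained benefit. Among participants seen at all visits the two do sum to the T1–T3 change, so a point estimate is recoverable. This also stands in part. The text still says that a difference, not its absence, decides the matter. Inferring retention from a non-significant T2–T3 result is weak, because non-significance does not show that nothing was lost.

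Three stronger readings are tempting, and the documents do not support them:

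- A reader might infer that the trial's whole long-term conclusion fails. The primary outcome is falls, recorded through the intervention and for 12 months after, and compared directly between the randomised groups. It does not use T2 as a baseline.
- A reader might infer that the trial will report no lasting effect, or harm from IR. The article has no rule that a null T2–T3 result means no lasting benefit, and a fading benefit looks like harm only if T2–T3 is read without T1–T2.
- A reader might infer that the contrast is not a randomised comparison because T2 follows treatment. D3 − D2 is a difference of two randomised comparisons; it is valid for retention but does not answer the question set for it.

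**Conclusion.** The point holds for the secondary outcomes: MDS-UPDRS motor section and full scale directly, and PDQ-39 and EQ-5D by extension, since they share the visits and the general statement under Assessments. The named contrast estimates the T3 effect minus the T2 effect and so cannot establish whether an effect is present 12 months after therapy. This is a stated choice that does not fit its purpose, not a detail left to another document.

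That the contrast is zero for a fully maintained benefit, and has the opposite sign for a partly maintained one, needs only groups comparable at T1, which randomisation gives in expectation. The power figures rest on the assumed effect sizes, correlations, equal SDs and 72 evaluable per group, and serve only as illustration. Severity: should be fixed for the secondary outcomes; not a must-fix for the trial, because the primary falls analysis is unaffected.

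**What to change.** Change three places in the protocol article's plan together, before analysis:

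- **Assessments and Outcome measures, Secondary:** define the longer-term effect as the between-group difference at T3 adjusted for the T1 value. The T1–T3 change is an acceptable alternative with the same expectation, but it is generally less precise. Keep T1–T2 for the immediate effect. Say explicitly that the same definition applies to the PDQ-39 and EQ-5D.
- **Statistical analysis, Secondary:** list that T3 comparison as a planned comparison, so that the long-term question is tied to a named test.
- **T2–T3:** report it with a confidence interval as a descriptive contrast of retention or decay that does not decide whether a long-term effect exists.

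The cost is a few sentences. All the data are already collected at T1, T2 and T3, and neither the sample size nor the visit schedule changes.
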